##### Saliva tests

Saliva samples will be collected with Salivettes without citric acid (Sarstedt, Nuembrecht, Germany) at specified times during in-clinic evaluations (Tables 4, 5, 6, 7). The cellulose dams will be gently moved around the mouth for 2 min and light chewing will be allowed. The loaded dams will then be returned to the original tubes before centrifugation at 1000 *g* for 2–5 min at room temperature. The clear saliva sample will be stored at −20°C until assay. Cotinine concentrations will be measured with a validated assay (Celerion, Lincoln, NE, USA).

##### Blood tests

Blood samples will be collected in blood-collection tubes. The blood volumes required for biomarker analyses and the biomarkers to be assessed are detailed in Table 10. Global gene expression profiles will be analysed with GeneChip expression arrays (Affymetrix, Santa Clara, CA, USA; [20]), which are accepted as an industry standard [21] and have been used successfully for clinical studies [22]. Any unused split samples will be transferred to the sponsor’s biological samples archive at the end of the study, at least until publication of the study results, to allow for any necessary repeat analyses.

**Table 10 T10:** Biomarkers in blood

**Biomarker**	**Collection tube volume and type**	**Matrix**
2-cyanoethylvaline	2 × 4.9 mL EDTA	Erythrocytes
4-ABP Hb adduct	2 × 4.9 mL EDTA	Erythrocytes
IL-6, IL-8, MCP-1, TNF-a, VEGF, MMP-1, MMP-9, TIMP-1, ox LDL, superoxide dismutase activity, glutathione peroxidase activity, glutathione reductase activity, catalase activity, Hb (lysate)	1 × 9 mL EDTA	Plasma, lysate
Total antioxidant capacity	1 × 4.7 mL serum	Serum
Ascorbic acid, dehydroascorbic acid	1 × 7.5 mL EDTA	Plasma
Neutrophil elastase, fibrinogen	1 × 5 mL citrate	Plasma
Hb (lysate), malondialdehyde	1 × 7.5 mL li-heparin	Lysate, cell pellet
sICAM-1	1 × 4 mL EDTA	Plasma
hsCRP (males)	1 × 8.5 mL serum	Serum
Lipid Profile	1 × 8.5 mL serum	Serum
LTB4	1 × 4 mL li-heparin	Plasma
White blood cells, neutrophils, monocytes, haemoglobin	1 × 2.7 mL EDTA	Plasma
Gene expression	2.5 mL × 2 Paxgene	Plasma

*4-ABP Hb adduct*, 4-aminobiphenyl haemoglobin adduct. *IL-6*, interleukin-6. *IL-8*, interleukin-8.

*MCP-1*, Monocyte Chemoattractant Protein 1. *TNF-a*, Tumor necrosis factor alpha.

*VEGF*, Vascular Endothelial Growth Factor. *MMP*, Matrix Metalloproteinase.

*TIMP-1*, Tissue inhibitor of metalloproteinases. ox *LDL*, oxidised low density lipoprotein.

*Hb*, Haemoglobin. *sICAM-1*, soluble intercellular adhesion molecule. *hsCRP*, high sensitivity C-reactive protein.

*LTB4*, Leukotriene B4. *EDTA*, Ethylenediaminetetraacetic acid.

#### Exhaled carbon dioxide

Expired carbon monoxide (CO) levels will be measured with the EC50 Micro III Smokerlizer CO meter (Bedfont, Maidstone, UK), or similar device at specified times (Tables 4, 5, 6, 7).

#### Mouth-level exposure to nicotine and tar

MLE to nicotine and tar will be estimated by a method developed and published by the sponsor [23]. A portion is cut from the mouth end of used cigarette filters collected from all cigarettes smoked over a 24 h period. The sponsor will provide the clinic with airtight collection tins for each participant, labelled with his or her identification code, for use during each in-clinic evaluation. Collected cigarette filters will be stored at room temperature until dispatch to the sponsor for MLE analysis (usually within 1 week).

At the sponsor’s laboratories, the filter tips will be placed in solvent and the extract will be analysed for nicotine content and ultraviolet absorbance to show the tar content. The data will be compared with calibration curves, obtained from machine-smoking regimes where smoke nicotine and tar yields are plotted against tip nicotine and ultraviolet absorbance values; the slopes of the curves represent the filtration efficiency of the cigarette filter. These filtration efficiency data and the amount of nicotine and tar retained on the cigarette filter will enable estimation of the amount of smoke that exited the filter and entered the smokers’ mouths during puffing (MLE).

#### Puffing, inhalation and exhalation measurements

Significant changes in smokers puffing and/or inhalation/exhalation behaviour following the product switch could affect the primary outcomes of this study. Therefore, puffing behaviour will be assessed in a normal smoking environment with the devices Smoking Analyser version 7 (SA7) and breathe in/breathe out (BIBO) apparatus, both of which have been designed, developed and produced by the sponsor and are described elsewhere [24]. The SA7 uses pressure transducers, built into a hand-held cigarette holder, to measure puff flow, volume and duration whilst the BIBO uses similar transducers in a second hand-held unit to measure inhalation/exhalation parameters. Both devices connect to a common-interface box and laptop computer where puffing and inhalation/exhalation behaviour is recorded.

Two cigarettes will be smoked per measurement through holders on the SA7 and BIBO apparatus. After each puff, drawn through the SA7 holder, participants will be asked to inhale and exhale up to five times through the BIBO. They will wear nose clips during the measurements but must try to puff, inhale and exhale as normally as possible. This system provides a complete record of the subject’s smoking behaviour, including puff volume, puff duration, number of puffs, total puff volume, mouth-hold duration, depth and time of inhalation and exhalation time.

Tests will be performed before and after switching for smokers in the switching groups and at similar time points for smokers in the non-switching groups. Owing to this study design allowing smokers to smoke when they wish, however, the specific timings of these measurements cannot be scheduled *a priori*, but attempts will be made to make the timings as close as possible on each measurement day for individual participants. The butts from the cigarettes smoked in these tests will be pooled with the others collected for the subject that day and sent to the sponsor for analysis.

#### Pulmonary function

Forced expiratory flow, forced expiratory flow in 1 s and peak expiratory flow will be measured at screening and once at the last in-clinic evaluation visit for every participant. Additional measurements will be obtained once in an in-clinic evaluation before switching and once during an in-clinic evaluation after switching in the smoking groups only.

#### Quality-of-life, sensory and diet and lifestyle assessments

Participants will be asked to self-administer study-specific questionnaires, written in German, on a tablet device during the in-clinic evaluation visits.

A prototype quality-of-life questionnaire, developed by an independent expert and funded by the sponsor , will be administered before switching and at the end of the study in the smoking groups, and in the middle and at the end of the study for the non-smoking groups. It will capture multi-dimensional data on individuals’ subjective perceptions on their daily lives, physical, psychological and social functioning, and well-being.

A second questionnaire will be administered to smoking groups before and multiple times after switching to assess participants’ sensory impression of the products and possibly assist in the interpretation of the toxicant exposure and compliance data. Questions take into account standard sensory attributes associated with cigarette smoking, including acceptability, draw effort, amount of smoke, satisfaction, irritation, nicotine impact, taste amount and quality, mouth dryness and aftertaste. Each attribute will be scored as magnitude and liking.

Aspects of an individual’s diet and lifestyle could affect the biomarkers under investigation in this study. Therefore, a third questionnaire will be administered to smoking and non-smoking groups and aims to provide an estimate of the participants’ normal standards of diet and lifestyle.

### Statistical analysis

The sample size estimate is based on observed data for BoE and BoBE and calculations made with MINITAB software version 15 (two-sample *t*-test). Percentages of reductions in smoke toxicants in the RTP versus commercial products are assumed to translate into corresponding reductions in BoE concentrations. Sample size calculations were performed to achieve a power of 80% to detect a difference between control and test products at an alpha level of 0.05. On the basis of the least sensitive BoE (aromatic amines), a sample size of 50 was determined to be adequate for all BoE of interest in this study (from study ISRCTN 72157335).

Similar estimates for BoBE are based on data for biomarkers in urine and plasma previously obtained by the sponsor and the least sensitive biomarkers in the literature, which showed that sample size of 50 would be adequate for BoBE in the primary objective. Literature search for secondary BoBE responses were uninformative, so sample size was assumed to be the same as for the primary outcomes.

On the basis of these calculations and a 6-week study in groups of 50 smokers (ISRCTN 72157335), it was estimated for this study that 70 participants per smoking group will be required to allow for anticipated attrition rates of up to 16% and achieve completion by at least 50 participants in each group. Sixty participants will be recruited to each of the ex-smokers and never-smoker control groups, as attrition is expected to be lower in these groups.

Statistical analyses will be performed by Celerion. A detailed statistical analysis plan will be prepared before database closure and agreed by the sponsor and Celerion. Any changes in the planned statistical methods will be documented in the study report.

The primary and secondary objectives will be examined by computing group biomarker levels at baseline, midpoints and at the end of the study (Table 1). Data for the primary outcome might be transformed to ensure that any assumptions associated with particular statistical tests or models are obeyed. ANOVA will be performed to identify differences between groups. As cigarette consumption may change over time or as a result of the switch, an ANCOVA will also be performed, using cigarettes per day as a covariate. For the secondary outcomes, an exploratory analysis with a matrix-type approach, such as principle component analysis, may be used.

A diagram summarising participant groups, group size and product switching is shown as Figure 2

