## Methods/design

### Study design

This study will be a single-centre, single-blind, controlled clinical trial with a forced-switching design that will be conducted in Hamburg, Germany. The study will be partly clinic-based (residential) and partly ambulatory (non-residential, including brief visits to the clinic). This study will be conducted in compliance with the ethical principles of the Declaration of Helsinki, Good Clinical Practice [17,18] and German law. When the Principal Investigator signs the protocol, he or she will be agreeing to adhere to the instructions and procedures described in it.

The Principal Investigator or designated investigators will ensure that participants are given full and adequate oral and written information in non-technical terms about the nature, purpose, potential risks and possible benefits of study participation. Participants will be given time to consider all the information, the opportunity to ask questions and will be required to read, sign and date informed consent forms that summarise the discussion before participating in any procedures related to the study.

The protocol and the informed consent forms have been approved by the ethics committee of the Ärztekammer Hamburg, Hamburg, Germany (Processing Number PV3824).

The study has a forced-switching design to enable data to be obtained about changes in exposure to tobacco smoke toxicants and related biological effects. The effects of RTP cigarettes will thus be evaluated within individuals (switching smokers serve as their own control) and between individuals (switching versus non-switching smokers). The ex-smoker and never-smoker control groups will provide background levels of BoE arising from environmental sources. They will also provide reference levels of BoBE that would be expected in people who have given up smoking for at least 5 years or who have never smoked. The inclusion of multiple types of non-smoker control groups is anticipated to improve the interpretation of the data generated in this study.

Financial compensation for the inconvenience to and effort of participants will be offered as part of the study, but the sponsor does not wish this approach to incentivise participants to smoke. Stipends will, therefore, be calculated independently by the clinic according to the usual rates for this type of clinical study and will be approved by the ethics committee of the Ärztekammer Hamburg.

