#### Withdrawal from the study

Participants will be allowed to withdraw from the study at any time. If they do so, they will receive a pro rata stipend. Investigators may at any time withdraw a participant from the study if they deem this action to be in his or her best interest or that of other participants. The end-of-study examination should be undertaken when a participant leaves the study, if he or she agrees, and reasons for withdrawal should be recorded. If patients cannot be assessed because he or she cannot be contacted after non-attendance of a scheduled event, they will be reported as lost to follow-up.

Participants will be informed of the importance of conforming to all requirements of the protocol, but violations might not result in removal from the study, as the sponsor realises that 100% compliance for every participant over the 6 month period of the study is unlikely. Honesty about protocol violations will, therefore, be encouraged. Participants will be asked to record and report at each clinic visit during ambulatory periods instances when they have not adhered to the protocol, or at check in for in-clinic evaluations. Investigators will decide whether non-compliant participants may remain in the study. Although withdrawals or dropouts are not expected to be replaced, the Sponsor will consider replacing participants to maintain the power of the study.

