### Investigational products

All study cigarettes will be provided by the sponsor free of charge (Table 3). To achieve blinding, unbranded cigarettes and packs will be manufactured specifically for the study. All packaging will include the mandatory health warnings, details of yields and tax stamps. The control cigarettes will match the specifications of the commercial cigarettes supplied before switching, except for a visual but cosmetic difference (i.e., plain white tipping on the control versus cork patterned tipping on the commercial cigarette; Table 3). This will allow RTP and control smoker cohorts to see a noticeable change to their cigarettes without being able to determine which product they are receiving. The different cigarette products will be identifiable to the clinic pharmacy staff and investigators by study identification codes (Table 3) that will be printed on the packaging and on the individual cigarettes. The cigarette products will be stored in a locked, limited-access area under controlled temperature and humidity conditions.

**Table 3 T3:** Investigational products

**Study period**	**Control group**	**Test group**
Days 1–14	Lucky Strike Silver (ID W861) with mono CA filter, cork-print tipping and commercial tobacco blend	Lucky Strike Silver (ID W861) with mono CA filter, cork-print tipping and commercial tobacco blend
	*Yields using ISO methodology: 7 mg tar, 0.6 mg nicotine, 8 mg CO*	*Yields using ISO methodology: 7 mg tar, 0.6 mg nicotine, 8 mg CO*
Days 15–183	Lucky Strike Silver (ID H285) with mono CA filter, white tipping and commercial tobacco blend	RTP (ID G429) with triple CA/CR20/charcoal filter^a^, white tipping and study tobacco blend (20% non-tobacco sheet, 50% treated tobacco and 30% commercial blend).
	*Yields using ISO methodology: 7 mg tar, 0.6 mg nicotine, 8 mg CO*	*Yields using ISO methodology: 7 mg tar, 0.7 mg nicotine, 8 mg CO*^*a*^

*ID,* study identification code, *CA,* cellulose acetate, *CR20,* amine-functionalised resin filter additive, *CO,* carbon monoxide, *RTP,* reduced-toxicant prototype cigarette, *ISO,* International Organisation for Standardisation. ^a^to be confirmed.

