##### Urine tests

Before the start of each 24 h urine collection period during in-clinic evaluations (Tables 5, 6, 7), each participant will be required to empty his or her bladder. Following this, each void will be collected in separate labelled brown plastic bottles and stored at 2-8°C. Collected urine will be pooled and stored at 2–8°C, labelled with the day on which collection ended. The total volume of urine collected over each 24 h period will be calculated from weight and specific gravity. After thorough mixing, samples will be transferred to labelled tubes and stored at −18 to −25°C. The details of biomarker assessments are shown in Table 9.

**Table 9 T9:** Urinary biomarkers

**Biomarker**	**Number and volume of aliquots**
4-Aminobiphenyl, 3-Aminobiphenyl,	2 aliquots of 12 mL each
o-Toluidine, 2-Aminonaphthalene	
OH-PAHs suite	2 aliquots of 12 mL each
Nicotine + 5	2 aliquots of 6 mL each
3-HPMA, HMPMA, CEMA	2 aliquots of 3 mL each
MHBMA	2 aliquots of 3 mL each
Total NNAL, NNN, NAB and NAT	2 aliquots of 10 mL each
F_2_-isoprostane (8-iso-PGF2 Type III)	2 aliquots of 6 mL each
F_2_-isoprostane (8-iso-PGF2 Type VI)	2 aliquots of 6 mL each
11-dehydrothromboxane B2	2 aliquots of 3 mL each
Urine mutagenicity	1 aliquots of 300 mL each
8-OHdG	2 aliquots of 1.5 mL each
Cis-thymidine glycol	2 aliquots of 1.5 mL each

*OH-PAH*, phenolic polycyclic aromatic hydrocarbons.*3-HPMA*, 3-Hydroxypropylmercapturic acid.

*HMPMA*, 3-hydroxy-1-methylpropylmercapturic acid. *CEMA*, 2-cyanoethylmercapturic acid.

*MHBMA*, monohydroxy-3-butenylmercapturic acid. *NNAL*, 4-(methylnitrosamino-1-(3-pyridyl)-1-butanol.

*NNN*, N-nitrosonornicotine. *NAB*, N-nitrosoanabasine. *NAT*, N-nitrosoanatabine.

*8-OhdG*, 8-Oxo-2′-deoxyguanosine.

Three haemoglobin adducts of identified smoke toxicants will be measured as BoED. Additionally, BoE that can yield information on short-term compliance, for example assessment of the ratio of a BoE for a smoke toxicant that does not change significantly between the products (such as nicotine) to a smoke toxicant that does significantly change (such as acrolein or NNK), will also be measured.

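### The claim of 80% power at 50 per group for all biomarkers of exposure cannot hold for exhaled CO, nor for a reduction in the nicotine markers, on the protocol's own yields

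*Protocol article*

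**What the plan says.** The Statistical analysis section bases the sample size on a two-sample t-test with "a power of 80% to detect a difference between control and test products at an alpha level of 0.05". The effect size comes from a rule: "Percentages of reductions in smoke toxicants in the RTP versus commercial products are assumed to translate into corresponding reductions in BoE concentrations". Aromatic amines are named as the least sensitive BoE, and on that basis "a sample size of 50 was determined to be adequate for all BoE of interest in this study". Seventy smokers per group are to be recruited, allowing for attrition of at most 16%, so that at least 50 per group complete.

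Table 1 lists among the primary BoE urinary nicotine, cotinine and 3-hydroxycotinine with their glucuronides, salivary cotinine and exhaled CO.

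Table 3 (Investigational products) gives the ISO yields of the RTP as "7 mg tar, 0.7 mg nicotine, 8 mg CO", marked to be confirmed. The control after the switch has 7 mg tar, 0.6 mg nicotine and 8 mg CO. The Urine tests section proposes a compliance ratio in which one side is "a smoke toxicant that does not change significantly between the products (such as nicotine").

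Two other statements bear on the rule. Under Study design, the ex-smoker and never-smoker groups "will provide background levels of BoE arising from environmental sources". Under Withdrawal from the study, the sponsor accepts that "100% compliance for every participant over the 6 month period of the study is unlikely".

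**The concern.** A power statement that covers all BoE needs an expected difference for each of them. The protocol's rule takes that difference from the smoke yields. For CO the listed yields are equal, and for nicotine the RTP yield is the higher one. The rule therefore supplies no difference for CO and no reduction for nicotine, and aromatic amines cannot be the least sensitive of the listed primary BoE.

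For BoE whose yields do fall, the rule is optimistic in two respects that the protocol itself mentions. The part of a BoE that comes from the environment does not respond to a change of cigarette, and a participant who sometimes smokes other cigarettes does not receive the full yield cut. Either would make the BoE fall by a smaller percentage than the yield.

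At stake is what the trial may claim about its sensitivity. Quoting 80% power beside a flat CO or nicotine result would give that result a meaning the design does not support. Such a result bears on whether smoke intake was comparable between groups.

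**Working it through.** **Inputs.** From Statistical analysis: 50 per group, 80% power, alpha 0.05, two-sample t-test, 70 recruited per smoking group, attrition of 16%. From Table 3: CO 8 v 8 mg, nicotine 0.7 v 0.6 mg. Sidedness is not stated; two-sided is assumed. The article gives no expected reduction, mean or SD for aromatic amines or any other BoE, so the figure of 50 cannot be reproduced and is inverted instead.

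**Step 1: what 50 per group can detect.** Normal approximation: d = (1.960 + 0.842) × √(2/50) = 0.560 SD. The exact t calculation gives 0.566 SD (0.501 if one-sided). As a percentage reduction this is 0.566 × CV: 17% at an assumed CV of 0.3 and 28% at 0.5.

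**Step 2: how many primary BoE are affected.** Nicotine, cotinine and 3-hydroxycotinine, each free and as glucuronide: 6. Salivary cotinine: 1. Exhaled CO: 1. Total 8. The other primary BoE are 3-HPMA, HMPMA, MHBMA and CEMA (4), tobacco-specific nitrosamine metabolites (4), aromatic amines (4) and PAH metabolites (9), together 21. So 8 of 29.

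**Step 3: apply the protocol's rule to them.**
- CO: 8/8 − 1 = 0%. The expected difference is zero, so the rejection probability is 5% whatever the sample size.
- Nicotine: 0.7/0.6 − 1 = +16.7%. There is no reduction to detect.

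**Step 4: allow for rounding of the yields.** CO listed as 8 mg could be 7.5 to 8.5 mg, so the true change lies between 7.5/8.5 − 1 = −11.8% and 8.5/7.5 − 1 = +13.3%. At −11.8%, power with 50 per group is 49%, 31% and 21% at assumed CVs of 0.3, 0.4 and 0.5. The nicotine ratio could lie between 0.65/0.65 = 1.00 and 0.75/0.55 = 1.36. At its most favourable end it is still not a reduction.

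**Step 5: sensitivity for BoE that are expected to fall.** Suppose the limiting BoE has exactly 80% power at 50 per group (d = 0.566), its SD is unchanged, and it falls by a fraction f of the yield cut. With background share b of the smoker's level and compliance c, f = (1 − b) × c. Neither b nor c is given, so f is an assumed range. Power is that of a two-sample t-test at effect f × 0.566. Completers at the planned attrition: 70 × 0.84 = 58.8, taken as 58.

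| f (assumed) | Power, 50 per group | Power, 58 per group | n per group for 80% |
|---|---|---|---|
| 1.0 | 80% | 86% | 50 (51 when rounded up) |
| 0.9 | 71% | 78% | 62 |
| 0.8 | 61% | 68% | 78 |
| 0.7 | 50% | 56% | 102 |

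**The case against.** The case on the other side has five parts.

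- **Table 3 holds machine yields and no biomarker values.** A reader might infer that it disproves a one-for-one fall of BoE with yield. It does not. The background section on earlier clinical studies and the Discussion both report that exposure fell after switching to such products, which supports the direction of the rule. What Table 3 contradicts is the extension of the power claim to all BoE.
- **The test is for a difference.** A reader might infer that no sample size is adequate for nicotine. That fails: a true +16.7% would be detected with 79% power at an assumed CV of 0.3 and 54% at 0.4, with 50 per group. The defect for nicotine is limited to a reduction, the direction the study hypothesis names. For CO it holds in full.
- **Changed puffing has no stated direction.** The section on puffing and inhalation says only that it could affect the primary outcomes, so it cannot be counted as weakening the reduction.
- **The attenuation figures are scenarios.** A reader might infer that the trial is shown to be underpowered. No background share or compliance rate is given, background need not apply equally to every BoE, BoE other than the limiting one may have spare power, and 58 rather than 50 completers are expected at the planned attrition.
- **Observed data and a descriptive objective.** The section already says that observed BoE data from the 6-week study were used, though not for which quantities. The primary objective is descriptive with no success rule per marker, so nothing shows that flat nicotine or CO results would be read as failures.

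All five stand as limits on the point. None removes the conflict over CO and nicotine. The phrase about BoE of interest might be meant to cover only BoE expected to fall, but the text does not limit it so.

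**Conclusion.** The point holds in a limited form. The statement that 50 per group is adequate for all BoE, with aromatic amines the least sensitive, conflicts with the protocol's own figures. On its stated rule, power for exhaled CO is 5% at any sample size. The seven nicotine markers have no expected reduction, in line with the Urine tests section, which treats nicotine as unchanged. Together these are 8 of 29 primary BoE. This rests on the listed RTP yields, which are rounded and to be confirmed. Even the most favourable rounding for CO leaves power at or below 49% for assumed CVs of 0.3 or more.

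For the remaining BoE the conclusion is weaker. The one-for-one rule leaves no room for background exposure or incomplete compliance, and the article shows no margin. The size of any loss is unknown; the table above is a range over assumed values and demonstrates no shortfall.

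**What to change.** In the Statistical analysis section:

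1. Limit the 80% power statement to BoE with an expected reduction.
2. State that nicotine and its metabolites, salivary cotinine and exhaled CO are not powered for a reduction. Report them as markers of comparable smoke intake, with a confidence interval for the RTP/control ratio. No equivalence margin is prescribed: the documents contain none, and with a listed nicotine ratio of 1.167 a formal equivalence test would need its own justification.
3. For the remaining BoE, make explicit that the stated power rests on BoE changes observed after switching in the 6-week study, giving the reduction and SD used for aromatic amines. If it rests on yields, show power as a sensitivity range at 50 and at 58 completers.
4. Check the CO and nicotine statements again once the RTP yields are confirmed.

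The cost is wording in the protocol and the analysis plan. No extra participants are needed, but the stated power becomes less favourable.

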***Biomarkers of biological effect***	
	• Urine: 8-OHdG, cis-thymidine glycol, 11-dehydrothromboxane B2
	• Blood: gene expression, neutrophil count, monocyte count
	• Erythrocytes: haemoglobin, superoxide dismutase activity, glutathione peroxidase, glutathione reductase, catalase activity, malondialdehyde
	• Plasma or serum: IL-6, IL-8, ascorbic Acid, dehydroascorbic Acid, total antioxidant capacity, hsCRP (males), fasting (12 h) lipid profile (total cholesterol, LDL, HDL, Triglycerides), fibrinogen, MCP-1, neutrophil elastase, MMP-1, MMP-9, TIMP-1, LTB4, TNF-α, VEGF, oxLDL

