### Study participants

#### Identification of study participants

Participants will be recruited into the study through advertisements on the clinic’s own website and local advertising that will not refer to the characteristics of the study products. All study participants (smokers and non-smokers) will be sourced from the Hamburg area from the same communities. Adult, healthy participants of either sex and of any ethnic origin will be enrolled. The planned ratio of male to female participants within each subgroup of the smoking groups is between 3:2 and 2:3, that is, an attempt will be made to enrol approximately equivalent numbers of male and female subjects into each subgroup, within these tolerances.

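### The 50 per group assumed for all secondary biomarkers of biological effect cannot apply to hsCRP, which is measured in men only

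*Protocol article*

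**What the plan says.** All references are to the protocol article.

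- **Statistical analysis**, method: "calculations made with MINITAB software version 15 (two-sample *t*-test"), chosen to "achieve a power of 80% to detect a difference between control and test products at an alpha level of 0.05".
- **Statistical analysis**, primary BoBE: a "sample size of 50 would be adequate for BoBE in the primary objective".
- **Statistical analysis**, secondary BoBE: "Literature search for secondary BoBE responses were uninformative, so sample size was assumed to be the same as for the primary outcomes". No marker is excepted.
- **Statistical analysis**, enrolment: "70 participants per smoking group will be required to allow for anticipated attrition rates of up to 16" per cent and "achieve completion by at least 50 participants in each group".
- **Table 1**, secondary biomarkers of biological effect: the plasma or serum list contains "hsCRP (males), fasting (12 h) lipid profile". **Table 10** (Blood tests) repeats the restriction of hsCRP to males.
- **Identification of study participants**: the planned male to female ratio "within each subgroup of the smoking groups is between 3:2 and 2:3".

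**The concern.** The sample-size statement is general, but one of the markers it covers is missing by design in every woman. The male restriction appears in two separate tables, so it reads as a deliberate choice and not a slip. The number available for hsCRP is then the number of men, which the planned sex ratio caps well below 50 per smoking group.

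What is at stake is how the hsCRP result is read. The section plans ANOVA to look for differences between groups. Someone who takes the sample-size paragraph at its word would judge an hsCRP comparison, and in particular an absence of difference, as resting on about 50 per group. It would rest on roughly half of that.

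**Working it through.** **Inputs**

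- Completers assumed for secondary BoBE: 50 per group (Statistical analysis).
- Enrolment 70 per smoking group, attrition up to 16%, completion floor 50 (Statistical analysis).
- Male share: 2:3 to 3:2 male to female, so 2/5 = 40% to 3/5 = 60% (Identification of study participants).
- Test: two-sample t-test, alpha 0.05, power 80% (Statistical analysis). The sidedness is not given; two-sided is assumed here.

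**The plan's own figure.** The 50 cannot be reproduced, because no effect size or SD is printed for any biomarker. It can only be solved backwards. Enrolment is more generous than the stated attrition needs: 50 / (1 − 0.16) = 59.5, so 60 would do, whereas 70 × 0.84 = 58.8 completers. The expected number of completers is therefore nearer 59 than 50.

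**Men available for hsCRP per smoking group** (completers × male share)

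| Scenario | Completers | 40% men | 50% men | 60% men |
|---|---|---|---|---|
| Completion floor | 50 | 20 | 25 | 30 |
| 16% attrition from 70 | 58.8 | 23.5 | 29.4 | 35.3 |
| No dropout | 70 | 28 | 35 | 42 |

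No cell reaches 50. To have 50 male completers a group would need 50 / 0.6 = 83.3, so 84 completers, up to 50 / 0.4 = 125. Only 70 are enrolled.

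**What the smaller number means for sensitivity.** The normal approximation to the standardised difference detectable with 80% power is (1.960 + 0.842) × √(2/n). At n = 50 this is 2.802 × 0.200 = 0.560 SD; the exact t-test calculation gives 0.566 SD. The table uses the t-test and takes 0.566 SD as the common yardstick.

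| Men per group | Detectable difference, 80% power (SD) | Power for 0.566 SD |
|---|---|---|
| 20 | 0.909 | 41.5% |
| 24 | 0.826 | 48.4% |
| 29 | 0.749 | 56.3% |
| 30 | 0.736 | 57.7% |
| 35 | 0.679 | 64.6% |
| 42 | 0.619 | 72.7% |
| 50 (as stated) | 0.566 | 80.0% |

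Hand check at n = 24: 2.802 × √(2/24) = 2.802 × 0.2887 = 0.81 SD by the normal approximation, against 0.826 by the t-test.

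**The case against.** **The analysis plan can deal with it.** It can decide how hsCRP is analysed. It cannot raise the number of men enrolled, and the size statement stands in the protocol. This is a statement that other parts of the same document contradict, not a missing detail.

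**Nothing is promised for hsCRP.** This has weight. The article openly says that the literature on secondary BoBE was uninformative and that the size was assumed, so it does not claim 80% power marker by marker. The objectives are descriptive, hsCRP is one of many secondary markers, and both tables print the male restriction beside it. That keeps the point small. It does not make the general size statement true for hsCRP.

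**Stronger readings that the document does not support**

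- A reader might take 20 to 30 men as the expected number. That is the completion floor; the lower end also needs the least favourable sex ratio. The stated enrolment and attrition give about 24 to 35, and the aim of roughly equal numbers of men and women puts the centre at about 29.
- A reader might take 41% to 65% as the power for hsCRP. The article gives no hsCRP effect or SD and does not say that 50 gives exactly 80% power for any secondary marker. The figures show only the relative loss against 50 per group.
- A reader might infer that the principal component analysis would lose every woman. The method is named only as an example that may be used. No variable list or complete-case rule is given, and choosing the variables is ordinary analysis-plan content. Several secondary items apply to smokers only (filter analysis, sensory testing, puffing), so some selection of variables is implied in any case. No finding can be built on this.

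**Conclusion.** The point holds, as a minor one. The size of 50 per group is carried over to all secondary BoBE, and for hsCRP it is unattainable under the article's own enrolment and sex ratio. The expected number is about 24 to 35 men per smoking group, with 20 to 30 at the completion floor and 28 to 42 with no dropout. This conclusion needs only the printed figures.

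The loss of sensitivity rests on three assumptions: a two-sided test, exactly 80% power at 50 per group, and the same standardised difference in men as in the whole group. On these, the detectable difference rises from 0.57 SD to about 0.68 to 0.83 SD at 24 to 35 men (0.91 SD at 20). Power for 0.57 SD falls to about 48% to 65% (41% at 20). No primary endpoint and no enrolment figure is affected.

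**What to change.** In Statistical analysis, after the sentence on secondary BoBE:

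1. State that the 50 per group does not apply to hsCRP, because it is measured in men only.
2. Give the expected number of men per smoking group (about 24 to 35 at 16% attrition, 20 to 30 at the completion floor).
3. Give the matching detectable difference (about 0.68 to 0.83 SD, up to 0.91 SD at 20 men), labelled as assuming a two-sided t-test at alpha 0.05 with 80% power and as not based on hsCRP data.
4. Say that hsCRP will be reported and interpreted as a men-only result with lower sensitivity than markers measured in both sexes.

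The cost is two or three sentences and a less favourable stated sensitivity for one secondary marker. No extra participants, samples or visits are needed.
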